## Abstract

Ocular microtremor (OMT) is a fixational eye movement that cannot be seen with the naked eye but is always present, even when the eye appears motionless/still. The link between OMT and brain function provides a strong rationale for investigation as there lies potential for its use as a biomarker in populations with neurological impairments. OMT frequency is typically 70-80Hz in healthy adults and research suggests that this will be reduced in those with neurological disease such as Parkinson’s Disease (PD). This study aims to examine OMT in people with PD compared to healthy older adults. This is an exploratory, observational study that will use a novel handheld device–The iTremor ONE, which has been developed to rapidly, non-invasively assess and evaluate OMT frequency. This device uses incident laser technology directed at the sclera. People with PD who meet the inclusion criteria will participate in a home-based assessment involving cognitive, motor (using the UPDRS-III) and OMT measures. With OMT as the primary outcome, assessment with the iTremor is quick, taking just three seconds to obtain a reading. People with PD will be invited into the laboratory to perform extensive cognitive assessments along with an assessment of balance, gait, and turning using wearable sensors. People with PD will be assessed both off, and on, their anti-parkinsonian medication following a 12 hour washout period. We will recruit 30 People with PD, 30 people with suspected PD and 30 age-matched healthy control participants for assessment of OMT. 20 People with PD will complete a test-retest reliability assessment at the same approximate time, exactly one week after their initial visit under the same conditions to explore consistency. This will be the first study of its kind to non-invasively investigate OMT frequency as a marker/monitor for PD with advanced technology that could be used within the clinic, laboratory, or home. Identifying OMT as a PD biomarker could better support clinical assessment, enabling improved provision of care to patients with advanced disease monitoring.

**Clinical trial registration:** This trial is registered at clinicaltrials.gov (NCT06051877; September 2023).

## Introduction

Parkinson’s disease (PD) is the second most common neurodegenerative disease and the world’s fastest-growing neurological condition [1], for which there are limited non-invasive biomarkers. PD is highly prevalent, with the mean age of onset being just 57 years-old and affecting ~2% of the world’s population over age of 60 [2]. PD is a progressive condition for which there is no known cause [3]. With the life expectancy rising globally, an increasing number of people are being diagnosed with PD and people with PD are living with their symptoms for longer. With this in mind, there is increasing pressure on healthcare services due to the progressive nature of the condition. Early intervention and monitoring of treatment response and disease progression through identification of biomarkers is essential [4]. The current method of diagnosis in PD is dependent on expert clinical judgement and there is a large subjective component. Dopamine transporter imaging (DaTSCAN) can also be used to confirm the diagnosis. DaTSCAN is an in-vivo, nuclear imaging technique which uses an IoflupaneI-123 injection to visually assess dopamine transporter density in the brain [5]. This, however, is invasive, expensive, time consuming and usually unpleasant for the patient. It requires a trained operator and can mean patients are put on a waiting list to get an appointment in addition to the initial wait to see the consultant.

Eye movements are well understood and provide an important insight to underlying neuropathology [6]. Eye movements have been identified as a likely biomarker for PD but there is no consistent, robust, and reliable gold standard method to objectively quantify these [7, 8]. Eye movement can indicate basal ganglia function [9], which is specifically relevant to PD due to the loss of dopamine in the substantia nigra. Anomalies are more evident in voluntary eye movements in the initial stages of PD whereas visually guided (reflexive, involuntary) saccades may also be involved in later stages [18] and deficits persist throughout disease progression [10]. In PD deterioration of dopaminergic mediated pathways in the BG causes overactive superior colliculus (SC) inhibition which in turn, prevents the SC from triggering the brainstem to generate saccades [11]. For example, pro-saccade performance (directing gaze towards a target) has been identified in predicting decline in PD, highlighting the potential benefits of accurate eye tracking in detecting these [2]. The difficulty of using eye movements as a marker of PD largely relates to the need for voluntary control of tasks, such as voluntarily moving the eyes towards or away from targets, which can become challenging due to the need to understand instructions. Additionally, there is much variation in the literature regarding the effects of dopaminergic medication on eye movements. This was illustrated in a study using a 12 hour ‘OFF’ period, comparing people with PD when they were ‘ON’ and ‘OFF’ their dopaminergic medication (in this case levodopa) which found that while there was high inter-subject variability, dopaminergic medication prolonged saccadic latency [7]. In other research, again using a 12 hour ‘OFF’ period, similar effects were reported showing that levodopa slowed reflexive pro-saccades (directing gaze towards a target), but the authors also reported improved voluntary anti-saccades (directing gaze in the opposite direction of target) [12]. In a more recent study looking at saccadic response to levodopa, participants refrained from taking their morning dose of anti-Parkinson’s medication [13]. They were tested upon arrival (OFF), following which participants then took their medications, waited 60 minutes, and were tested again (ON). Here authors reported that pro-saccadic latency was prolonged by dopaminergic medication in PD but that no other statistically significant change was observed in any other saccadic parameters [13]. Consequently, involuntary eye movements may provide a useful biomarker for PD that is responsive to dopaminergic medication. Testing using ON and OFF periods with dopaminergic medication has been extensively performed in research with no detrimental effects to the individual. The existing evidence for eye movement response to dopaminergic medication therefore provides rationale for investigating involuntary eye movements in an ON and OFF state utilising a 12 hour ‘OFF’ period that has previously been described in similar eye movement research.

Ocular micro tremor (OMT), first described in 1934, is an involuntary eye movement that is present even when the eye is apparently still [14]. OMT is considered a fixational movement and is a constant small amplitude, high frequency tremor of both eyes which goes unnoticed by the individual and cannot be seen by the naked eye [15]. OMT has been linked to the constant activity of the extra-ocular muscles stimulated by impulses from oculomotor neurons found in the brainstem [15–19] and thought to be related to tonic neural discharges. Clinical use of OMT has been explored in cases of PD [20], Multiple sclerosis [21], brainstem death [17] and, measuring depth of anaesthesia [22, 23]. OMT frequency is historically measured using the piezoelectric method [24]. In those with neurological disease and impairment, OMT frequency is reported to be reduced compared to healthy controls [17, 20, 21, 25]. OMT frequency is also known to be affected by alcohol [26], caffeine [27] and age [28]. Whereas, time of testing [26] and gender [29] have not been found to affect OMT and no differences have been found between left and right eye readings [30]. When reviewing findings on OMT, a study described the frequency of OMT to range from 70 – 130Hz in healthy individuals [29]. However, it is suggested that discrepancies in the estimated normal frequency of OMT oscillations seen in the literature are likely due to lack of an efficient gold-standard technique for measurement meaning methods differ between studies [24, 31]. Previous work has illustrated that OMT frequency declines with age, with the authors indicating normal OMT values are different for those over the age of 60 years [28].

Neurological disease also significantly decreases OMT frequency when compared to healthy controls. For example in PD, a study reported a mean OMT frequency of 67.68Hz (Healthy range = 70 – 130Hz [29]). In another study focusing on OMT and idiopathic PD, authors observed two groups–an ON group and OFF group [20]. These were determined using the bradykinesia subsection of the Webster Scale [32]. A score of 0 or 1 was considered ON (n = 12), and a score of 2 or 3 was considered OFF (n = 10). The healthy controls in this study had a mean OMT frequency of 81.64Hz (SD = 6.10) and both PD ON, and PD OFF, groups exhibited significantly lower OMT frequencies of 73.78Hz (SD = 5.55) and 58.88Hz (SD = 10.35) respectively; the mean frequency of the OFF group was significantly lower than that of the ON group. This preliminary evidence suggests that People with PD have reduced OMT, thus supporting the need for more robust evidence.

PD related motor symptoms tend to only be noticed when there has been a ~80% depletion of striatal dopamine and so identification of the disease using OMT as an objective measure could benefit prognosis and likely help identify subtle changes in the early stages [33]. Observing OMT through multiple recordings in patients in an ON and OFF state could yield insight to individual responsiveness to dopaminergic medication. Exploring OMT as a biomarker for PD using accessible novel technology could facilitate an objective diagnosis and monitoring of the disease and it’s progression [24]. Overall, this presented protocol aims to examine OMT as a potential marker for PD and for disease monitoring. To achieve this, the following aims are outlined:

Analytical Validation: (1) Investigate the test-retest reliability of the iTremor ONE device in measuring OMT frequency (Hz) in People with PD; (2) Investigate the feasibility of measuring OMT using a hand-held device in a real-world clinical setting. This will cover the reliability and feasibility of OMT measurement in People with PD.

Clinical Validation: (1) Compare OMT frequency in People with PD and age-matched controls, and suspected PD patients; (2) Explore relationships between OMT measurement in People with PD and other clinically relevant outcomes (e.g., UPDRS); and (3) Examine the effect on OMT of dopaminergic medication in PD. This will cover known groups validity, convergent/divergent validity and response to a known intervention in People with PD.

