### Participants

#### Step 1) Recruitment

Participants will be a volunteer sample recruited from Northumbria Healthcare NHS foundation Trust. Participants will be seen in clinic by a Movements Disorders specialist at these sites where people are referred for suspected PD diagnosis, and those with diagnosed PD will be identified. Potential participants will be invited to consider the study and referred to the investigators who will attend the clinics. Healthy controls could include spouses/ siblings/ other volunteer older adults. We will recruit healthy older adults from advertisement using posters, which will be placed within neurology and geriatric departments. We will also recruit older adult and PD participants from previous or ongoing studies at Northumbria University where the participant has given written informed consent to be contacted regarding future research studies, and from local PD support groups.

*Inclusion / Exclusion criteria*. PD participants will be included if they have a diagnosis of PD according to UK brain bank criteria. PD and older adult participants will be excluded if there is any psychiatric co-morbidity, a history or evidence of head injury or ocular disease (such as cataracts), they have a clinical diagnosis of dementia or other severe cognitive impairment (measured using the MoCA with a cut off score of <21). For those involved in Step 3 of the project, PD participants must be consistently taking dopaminergic (‘anti-Parkinson’s’) medication.

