#### Step 2) Lab assessment

We will recruit 30 confirmed PD, 30 suspected PD, and 30 age-matched healthy control participants for laboratory and home-based assessment of OMT (Fig 1). As this is a pilot study of a novel OMT measurement device and we are interested in the feasibility of measuring OMT in a real-world clinic setting rather than determining efficacy of OMT for differential diagnostics in PD within clinical settings, a formal sample size calculation was not conducted. We have based the sample size on previous studies of eye-tracking in PD that have used samples <30 per group and found significant differences compared to controls [34].

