#### Step 2: Laboratory assessment (Suspected PD, confirmed PD and HC groups)

*Demographics*. The participant will then be interviewed by a member of the study team. The interview will include questions regarding education level, falls history, current medications, history of head injury, activity level, and side dominance as well as basic demographics such as age and gender. We will ask participants for their medications currently used (so that we can calculate the levodopa equivalent daily dosage (LEDD) [37, 38].

*Cognitive assessment*: Participants will also undergo a battery of cognitive, motor, and visual assessments. The cognitive assessments should last around 30 minutes and consist of a series of pen and paper tasks which the participants will be guided through by a member of the research team. Global cognition is assessed using the Montreal Cognitive Assessment (MoCA) [39]. Benton’s Judgement of Line Orientation test assesses visuospatial skill (JLO) [40]. The trail making test of visual attention (TMT A and B) is used to assess executive functioning [41] as well as Royall’s Clock Drawing task (CLOX 1&2) [42]. Forward digit span [43] is used as a measure of working memory. Participants will also complete a series of computerised tests to assess attention using a button pressing task. This attention battery is a valid means of testing attention and has been implemented in previous studies involving People with PD [44].

*Visual assessment*: The visual assessments are conducted binocularly before using an eye occluder to measure for the left and right eyes independently. The visual assessments should take 10 minutes to complete.

*Visual acuity—LogMAR*. This test is a simple visual test to assess participants ability to read at a distance. The Logarithm of the Minimal Angle of Resolution (LogMAR) is used as a standardised binocular measure. Participants are seated at a 4-meter distance from the chart and asked to read the letters aloud from left to right starting at the top left. The participant is stopped if two incorrect letters are given. LogMAR is calculated using the following formula: LogMAR = (score of the line before termination)–(0.02 x the number of errors) + (0.02 x correct answers before terminal line). A LogMAR score of 0.00 is equivalent to 6/6 (20/20) vision. The LogMAR charts are scored by letter instead of row making them a more precise measure of visual acuity.

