#### Step 3a: Home-based assessment (Confirmed PD only)

Within ~1 month of Step 2, participants will be asked to abstain from their dopaminergic medication overnight for 12 hours, and researchers will attend their home in the morning prior to their morning dose, to conduct the home-based testing.

*Conducted in OFF medication state*. We will collect the following details when OFF medication: MoCA and UPDRS-III.

*Conducted in OFF and ON medication states*. *OMT*: OMT will be measured using the iTremor Device in the same manner as Step 2 (see above for details). OMT testing will be conducted immediately when attending the home (OFF state, after 12hours medication withdrawal), and then again 60 minutes after the participant has taken their usual dopaminergic medications.

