To examine whether OMT can differentiate PD from age-matched controls, we will use an ANOVA, with group (PD vs control) as a between-subject factor. Again, to adjust for covariates (i.e. disease severity/ cognitive function), we will use analysis of covariance (ANCOVA). Receiver operating characteristic (ROC) curve analyses will also be used here to determine the relative sensitivity and specificity of OMT for differentiating People with PD and healthy controls. This provides AUC which is a metric to evaluate the classifiers output quality.

*Clinical validation aim II*. *Convergent / Divergent validity*: Pearson’s correlations will be used to detail the relationships between OMT measurement and other clinically relevant outcome measures, such as the UPDRS or MoCA.

*Clinical validation aim III*. *Known intervention response*: To examine whether OMT reduces when in the OFF-medication state in PD, we will use an ANOVA with medication-state (ON vs OFF medication) as repeated measures.

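### The protocol says age, caffeine and alcohol affect OMT, but age is missing from the stated covariates and the published procedure neither standardises nor records caffeine or alcohol

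*Protocol article*

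**What the plan says.** The Introduction names three influences on the primary outcome: "OMT frequency is also known to be affected by alcohol [26], caffeine [27] and age [28". For age it gives a direction and a threshold of 60 years, but no slope: "Previous work has illustrated that OMT frequency declines with age, with the authors indicating normal OMT values are different for those over the age of" that threshold. It also says that "time of testing [26] and gender [29] have not been found to affect OMT".

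- **Design.** Under Step 2, "We will recruit 30 confirmed PD, 30 suspected PD, and 30 age-matched healthy control participants for laboratory and home-based assessment of OMT". Only the healthy controls are called age-matched. Under Step 1, "Healthy controls could include spouses/ siblings/ other volunteer older adults".
- **Data collected.** The Step 2 interview covers "basic demographics such as age and gender", current medications and other items. Caffeine and alcohol are not among those listed.
- **Procedure.** The OMT assessment covers seating, headrest, glasses, gaze target and blinking. The only abstention stated is the overnight one from dopaminergic medication in Step 3a. OMT is read on arrival (OFF) "and then again 60 minutes after the participant has taken their usual dopaminergic medications" (ON). Step 3b repeats the visit time and the medication time one week later.
- **Analysis.** Confirmed versus suspected PD is a one-factor ANOVA, followed by a ROC for PD versus other diagnosis. PD versus control is an ANOVA, with an ANCOVA "to adjust for covariates (i.e. disease severity/ cognitive function"). ON versus OFF is a repeated-measures ANOVA with medication state as its only factor.

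**The concern.** A factor that the protocol accepts as moving the primary outcome should be balanced by design, held constant, or measured and adjusted for. Here this is done in part for age and not at all for caffeine or alcohol.

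The stakes differ by comparison:

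- **Confirmed versus suspected PD, and the diagnosis ROC.** If the groups differ in age, the age-related fall in OMT is read as a difference in disease status.
- **PD versus control.** Matching protects this contrast to the extent that it succeeds. Leaving the matching variable out of the model keeps any residual imbalance and gives up precision.
- **ON versus OFF.** The order is fixed, so anything that changes between the two readings is attributed to medication. Caffeine during the 60-minute morning wait is the plausible candidate.
- **Retest.** Differing intake at the two visits adds within-person variation, which would tend to lower the ICC and widen the limits of agreement.

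**Working it through.** The plan has no sample size or power figure to reproduce. The check has two parts.

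**1. What the published plan does with each factor**

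| Factor | Effect on OMT per Introduction | Design or procedure | Recorded | In a model |
|---|---|---|---|---|
| Age | Yes, declines | Matched for healthy controls only | Yes | Not named |
| Caffeine | Yes, direction and size not given | Nothing stated | Not listed | Not named |
| Alcohol | Yes, direction and size not given | Nothing stated | Not listed | Not named |
| Time of testing | Not found | Same visit time at retest | n/a | Not named |

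The plan therefore standardises one condition that it reports as having no effect, and leaves two that it reports as having one.

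Age is constant within a person on one morning, so it cancels from ON minus OFF. Alcohol matters less there than caffeine because both readings fall on the same morning.

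**2. How sensitive the tests are to an uncontrolled shift**

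Inputs from the study cited in the Introduction: controls 81.64 Hz (SD 6.10), PD ON 73.78 Hz (SD 5.55), PD OFF 58.88 Hz (SD 10.35). From the protocol: 30 per group and two-sided 5%. The shift b is assumed, because the documents give no effect size.

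*Between groups*

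- Pooled SD = √[(6.10² + 5.55²)/2] = 5.83 Hz
- SE = 5.83 × √(2/30) = 1.51 Hz
- Rejection probability with no true difference = Φ(b/SE − 1.96) + Φ(−b/SE − 1.96)

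| Assumed shift b | False rejection |
|---|---|
| 0 Hz | 5% |
| 1 Hz | 10% |
| 2 Hz | 26% |
| 3 Hz | 51% |

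For example, if recent caffeine moved OMT by 5 Hz (assumed) and its use differed by 25 percentage points between groups (assumed), b = 5 × 0.25 = 1.25 Hz and false rejection is 13%.

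No SD is given for suspected PD. Applying these figures to confirmed versus suspected PD assumes a similar SD.

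*ON versus OFF, paired, n = 30*

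- SD of the difference = √(5.55² + 10.35² − 2r × 5.55 × 10.35)
- The cited ON and OFF values come from separate groups, so the within-person correlation r is assumed.

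| r | SD of difference | SE | False rejection at an assumed mean shift of 2 Hz |
|---|---|---|---|
| 0.3 | 10.17 | 1.86 | 19% |
| 0.5 | 8.97 | 1.64 | 23% |
| 0.7 | 7.58 | 1.38 | 30% |

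*For scale.* The cited differences are 81.64 − 73.78 = 7.86 Hz (control versus ON) and 73.78 − 58.88 = 14.90 Hz (ON versus OFF). A shift of 1 to 3 Hz would not by itself explain either. It could create or distort a smaller difference, and it could distort the ROC results.

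**The case against.** The strongest reply is that this is a condensed article on an exploratory pilot. Test-day instructions and case-report fields usually sit in the full protocol, and the final covariate list in the analysis plan. The interview list need not be exhaustive. The ANCOVA sentence reads as though an earlier adjustment had been described, so adjustment may also have been meant for confirmed versus suspected PD. The abstract says that the retest is done under the same conditions. Some natural variation is expected in a study of real-world feasibility.

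Part of this stands. Whether the full protocol restricts or records intake cannot be known from the article, so the point is limited to the published procedure. The missing detail on how controls are matched is not a finding.

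It does not remove the point. The article does state a covariate list, worded as complete rather than as examples, and age is not in it. It also states a one-factor model for confirmed versus suspected PD. The OMT procedure is described closely enough to mention glasses and the headrest, and the same conditions at retest are spelled out only as visit time and medication time. An analysis plan written later cannot recover intake that was not recorded at the visit.

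A reader might go further in three ways that the documents do not support:

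- **That age is uncontrolled throughout, or biases ON-OFF.** Controls are age-matched by design, and age cancels within a person. Recruiting spouses, siblings and volunteers says where controls come from, not that matching fails.
- **That a drink necessarily coincides with medication state.** This holds only for caffeine taken between the two readings. A participant may drink before the OFF reading, after both, or not at all.
- **That an age bias of a known size exists.** An assumed slope of 0.2 to 0.5 Hz per year and a 4-year gap would give 0.8 to 2.0 Hz, but neither input is in the documents.

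**Conclusion.** The concern holds in a limited form. Age is matched for the healthy controls only. It is not a stated covariate, and no matching or adjustment is stated for confirmed versus suspected PD or for the diagnosis ROC. Caffeine and alcohol, which the protocol says affect its primary outcome, are not restricted, recorded or adjusted for in the published procedure. The fixed OFF-then-ON order means that caffeine taken between the readings could not be told apart from a medication effect.

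The direction and size of any bias cannot be derived from the documents. The figure of about 26% false rejection is a sensitivity result. It rests on an assumed 2 Hz shift, the cited SDs and 30 per group, and it is not an estimate of what will happen. If the true differences are as large as those cited, shifts of this order would not change the conclusions. They matter if the differences are smaller.

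**What to change.** 1. Include age, as a continuous covariate, in every between-group OMT model, including confirmed versus suspected PD. Report the diagnosis ROC with an age-adjusted version beside it.
2. Record last caffeine and alcohol intake at each OMT reading.
3. Keep caffeine conditions the same across the OFF, ON and retest readings.
4. Use recorded intake as a covariate or in a sensitivity analysis. Excluding everyone with any intake could remove a large share of 30 per group, so adjustment may be the more workable choice.

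**Cost.** Age is already collected and uses one degree of freedom. If it explains 10% to 20% of OMT variance (assumed), the SE is multiplied by √0.90 = 0.95 to √0.80 = 0.89, so there is a gain even where matching succeeds. Recording intake needs two case-report fields and one line of participant instructions, with minor inconvenience to participants. Recruitment began in June 2023, so participants already assessed will lack the intake fields and may have been measured under different conditions. The report should give their number and say so.
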